**Exclusion criteria**	
Participants who have signs of preeclampsia on initial evaluation	Preeclampsia (BP reading > 140 mmHg and/or 90 mmHg on at least 2 occasions after 20 weeks’ gestation accompanied by evidence of end-organ involvement)
Multifoetal pregnancy	
Lethal foetal abnormality	Lethal foetal chromosomal, genetic or morphological abnormality detected on screening tests
Inability to access or use the app-based system	
Unable to consent	
Non-English speaking background not supported by the mobile application	

*GFR* glomerular filtration rate, *SLE* systemic lupus erythematosus, *BP* blood pressure, *HDP* hypertensive disorder of pregnancy

Participants will be recruited through both the antenatal and specialist obstetric medicine clinics. Eligible patients will undertake full informed written consent with an Obstetric Physician or research midwife. Consented participants will be randomised in a 1:1 ratio, to receive either conventional care with face-to-face consultations or remote BP monitoring. Computer-generated randomisation will occur through RedCAP™, and a minimisation protocol for the variables chronic hypertension, centre of treatment and aspirin use will be instituted. Individual patient randomisation will be used so that treatment allocation remains unpredictable. To avoid bias, the random allocation sequence is concealed from those responsible for recruiting women into the study, and generated by the REDCap randomisation module. A research midwife based at each site will be responsible for consenting and assigning participants to the trial arms. Blinding of the treatment allocation to the patient and treating physician will be difficult and unethical. Outcome assessors and data analysts will not be blinded to treatment allocation. An overview of the study procedures is shown in Fig. 1.

**Fig. 1 Fig1:**
[figure not shown]
Schedule of enrolment, interventions, assessments and overview of study flow

#### Intervention arm: remote monitoring of BP

Prior to the start of the study, we will provide training of the remote monitoring strategy at each site to ensure familiarity with the technological aspects. A research midwife at each centre will be trained how to register, train and enrol new participants on the novel platform (consisting of an automated blood pressure device connected via Bluetooth to a smartphone application) after randomisation. As set in the research protocol, responsibilities of the clinicians will include review of uploaded parameters, management after reviewing new results and telephone contact with the pregnant women at home.

Women randomised to remote monitoring will be provided with an automated BP machine validated for use in pregnancy and preeclampsia (iHealth Track), which uploads blood pressure readings to a smartphone application (M♡THer). They will be educated on its use at their first visit by a research midwife or investigator. The smartphone application and innovative platform (M♡THer), was developed by the Commonwealth Scientific and Industrial Research Organisation (CSIRO) Australian e-Health Research Centre (AEHRC) and has been found to be feasible in supporting remote monitoring of women with diagnosis of gestational diabetes [39]. For this trial the application has been customised to focus on BP monitoring.

Education will be provided through a standardised video created by the trial team in addition to a patient information sheet with telephone contact numbers for technical or health-related questions. Participants will have any questions about the intervention answered.

Participants will be asked to take 3 readings, 5 min apart while sitting quietly at any time of the day. The first reading will be disregarded, and the higher of the last two readings will be recorded. This will occur on 3 occasions every week. The blood pressure reading, in addition to a symptom check-list through the M♡THer application, will be uploaded to a secure web-based dashboard. A pre-specified evidence-based algorithm built-in to the M♡THer application (Table 2), consistent with NICE guidelines for BP targets in pregnancy [2], will provide instructions to the patient. Patient data uploaded to the dashboard will be reviewed three times a week by an obstetric medicine clinician. Possible steps in the management, after the uploaded results are checked are (1) expectant management, (2) titration of medications by telephone call, (3) participant booked to attend a Telehealth appointment with the Obstetric Medicine clinic, (4) same-day clinical assessment or (5) hospital admission. Should hospital admission be necessary due to clinical deterioration, the patient will be monitored in the hospital as per local protocol and all relevant data will be collected. If discharged, women will continue remote BP monitoring until 6 weeks postpartum. All events of healthcare utilisation including imaging, pathology tests, consultations in the outpatient department and community-based care as well as ward admissions will be recorded.

**Table 2 Tab2:**
[figure not shown]
In-built prespecified blood pressure algorithms

#### Control arm: usual care

Women in the control arm will have their blood pressure monitored in face-to-face consultations, and initiation and/or adjustment of medication (where appropriate) based on these measurements at the discretion of the Obstetric or Obstetric Medicine physician. The frequency of these specialty appointments will be dictated by clinical need as well as local current practice, but will follow the minimum schedule of at least 6 outpatient appointments, in addition to the routine antenatal schedule (Fig. 2). Women will return to the clinic for follow-up at 6 (+ / − 2) weeks postpartum.

**Fig. 2 Fig2:**
[figure not shown]
Participant timeline

Increasingly, women are utilising home blood pressure monitoring during pregnancy. However, the interpretation of these blood pressure readings is left to the patient, without clear guidance on normal and abnormal values in pregnancy. Our trial aims to evaluate the effectiveness and safety of remote blood pressure monitoring. Remote blood pressure monitoring in this trial refers to not only home blood pressure monitoring, but also a system whereby readings are transmitted to clinicians for review, in addition to immediate interpretation for patients about normal and abnormal values in the context of pregnancy, founded on evidence-based guidelines. This allows for proactive, rather than reactive care.

Therefore, as a pragmatic trial, women within the control arm may still undertake home blood pressure monitoring but are not encouraged to do so. This would fall within the scope of conventional care as defined in the trial protocol. For participants within the usual care arm who undertake home blood pressure monitoring using their own devices, decisions about clinical care will not be made based on home blood pressure readings provided by the patient in between appointments. However, for participants who report hypertension measured at home, usual clinical practice would be followed. Clinicians would validate this through more regular clinical visits, undertaking appropriate investigations and a formal blood pressure assessment in the fetomaternal assessment unit. Participants will also be advised that should they have clinical concerns, they should present to their local birthing unit for assessment.

Standard of care with regards to all other aspects of their antenatal care will be otherwise instituted for both groups including early initiation of low dose aspirin (LDA). Compliance with LDA will be assessed through obtaining a platelet function analyser (PFA-100) assay between 20 and 23 weeks’ gestation [4]. A routine set of pathology including full blood count, renal function testing, liver enzymes and maternal protein-creatinine ratio will be undertaken at 28 weeks’ and 36 weeks’ gestation. All women will be reminded to report, between and at routine antenatal visits, any new symptoms consistent with possible pre-eclampsia. If there are concerns regarding the development of preeclampsia, a minimum set of investigations will include a full blood count, renal function testing, liver enzymes, a maternal urine protein-creatinine ratio and soluble fms-like tyrosine kinase-1 to placental growth factor ratio (sFLT-1/PlGF ratio). Foetal assessment will be undertaken by measurement of foetal heart rate and pattern using a cardiotocography (CTG) and, if indicated, detailed ultrasonographic assessment. The remainder of antenatal care, in particular the timing and mode of delivery will be undertaken as per local practice. No concomitant treatments are prohibited during the trial.

### Outcome measures

The primary outcome is perinatal mortality and morbidity, represented by a composite adverse foetal outcome. The composite adverse foetal outcome is defined as: perinatal loss (miscarriage, pregnancy termination, stillbirth or neonatal death), high-level neonatal care (admission to neonatal intensive care unit or special care nursery for > 48 h) or small-for-gestational age (birthweight below the 10th centile). All components of the composite outcome will be assessed separately individually as secondary outcomes. Other secondary outcomes will consist of maternal outcomes, feasibility and patient satisfaction, quality of life, healthcare utilisation and cost-effectiveness (Table 3).

**Table 3 Tab3:** Secondary outcomes

*General*
Rate of composite maternal complications (adapted from the International Collaboration to Harmonise Outcomes for Pre-eclampsia [40]: - Maternal mortality - Eclampsia - Stroke -Cortical blindness - Retinal detachment - Pulmonary oedema - Acute kidney injury - Liver capsule haematoma or rupture - Placental abruption - Postpartum haemorrhage - Raised liver enzymes - Haemolysis - Low platelets - Admission to the intensive care unit - Intubation/mechanical ventilation
Gestational age at delivery
Birthweight
APGAR scores at 1 min and 5 min
Neonatal seizures
Neonatal respiratory morbidity
Uncontrolled hypertension
Pregnancy prolongation
Rate of preeclampsia
Rate of induction of labour
Mode of delivery
Postnatal readmission rate
Second trimester mean systolic and diastolic BP
Third trimester mean systolic and diastolic BP
Postnatal mean systolic and diastolic BP
Mean systolic and diastolic BP obtained in clinic setting
Area under the BP curve
Proportion of readings within target (< 140/90 mmHg)
Episodes of severe hypertension > 160/100 mmHg
Time to medication institution (weeks’ gestation)
Number of medication dose escalations

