	**Definition**
**Inclusion criteria**	
Age ≥ 18 years	
Able to provide informed consent	
Able and willing to follow instructions for use of automated BP machine and app-based system	
Chronic kidney disease	Abnormalities of kidney structure or function (either reduced GFR < 90 ml/min/1.73 m^2^, albuminuria or proteinuria) present prior to pregnancy
Autoimmune disorder	Diagnosis of an autoimmune condition such as systematic lupus erythematosus prior to pregnancy
Type 1 or type 2 diabetes mellitus	
Chronic hypertension	Systolic BP > 140 mmHg or diastolic BP > 90 mmHg on at least 2 occasions prior to 20 weeks’ gestation
Previous pregnancy complicated by HDP or diagnosis of gestational hypertension this pregnancy	Previous HDP includes chronic hypertension, gestational hypertension, preeclampsia, or preeclampsia superimposed on chronic hypertension Gestational hypertension (Systolic BP > 140 mmHg or diastolic BP > 90 mmHg on at least 2 occasions after 20 weeks’ gestation)
Confirmation of viable intrauterine pregnancy on dating scan	
IVF pregnancy	
High-risk for developing preeclampsia on first-trimester screening	Reported risk of < 1:100 of developing preeclampsia on commercially available combined first-trimester screening tests
Before 28 weeks gestation	

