### Data handling, analysis and result reporting

At study entry, baseline demographics, medical and obstetric history will be collected. Antenatal data pertaining to the secondary outcomes will be collected throughout gestation including blood pressure data, investigations undertaken and any contact with the healthcare system. For the interventional arm, the M♡THer application will collect blood pressure data, symptom checklists and weight. At delivery, relevant data will be collected from the electronic medical record for the assessment of foetal outcomes such as gestational age at birth, birth weight, Apgar scores, and high-level neonatal care admission. For maternal outcomes, data will be collected from the electronic medical record on mode of delivery, antihypertensive medication use and adverse outcomes. Standardised online case report forms developed by investigators through REDCap™ will be used, and data will be stored on password-protected cloud drives located behind a university firewall, available only to investigators.

Data analyses will primarily be carried out according to the intention-to-treat principle but we will also perform per protocol analyses excluding participants in whom there is a clear deviation of the intended care as prescribed by the protocol in either the control group or the remote monitoring group. We will undertake both analyses with and without imputed data. We anticipate that some patients within the conservative care arm will undertake home blood pressure monitoring using their own devices. In such cases, we will ensure that during consultations, changes to medications will not be made based on home blood pressure readings provided by the patient. However, if there are clinical concerns, we would advise participants in the conventional arm to be assessed in the local birthing unit as is current standard of care. The case reporting form will take note of patients who are part of the conservative care arm that own blood pressure machines, and this will be adjusted for in a sensitivity analysis as a potential confounder.

Results will be reported according to Consolidated Standards of Reporting Trials (CONSORT) guidelines, using the extension for non-inferiority trials [44].

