The dichotomous primary outcome will be analysed using a generalised linear model (with binomial distribution and log link), adjusting for minimisation variables, chronic hypertension and aspirin use. Treatment effects will be expressed as adjusted risk ratios with 95% CIs. The secondary outcomes that are binary will be analysed using the same methods described for the primary outcomes, with corresponding 95% CIs. For those secondary outcomes that are continuous, data that is normally distributed will be analysed with parametric tests and non-normally distributed data will be analysed with non-parametric tests. Significance will be set at 0.05 and adjustments for multiple comparisons will be made where comparing several groups.

Subgroup analyses will be undertaken on (i) variables used in the minimisation algorithm (i.e. hypertension type [chronic or gestational hypertension] and LDA use); and (ii) other variables of prognostic significance pre-specified as ethnicity, body mass index, prior severe hypertension in the index pregnancy, antihypertensive therapy at randomisation, gestational diabetes mellitus at randomisation, and smoking status at randomisation. Subgroup analyses will be limited to the primary outcome. Results will be presented as adjusted risk ratios with 95% confidence intervals. The results of subgroup analyses will be treated with caution and will be used for the purposes of hypothesis generation only.

Participants with missing primary outcome data will not be included in the primary analysis in the first instance. This presents a risk of bias, and sensitivity analyses will be undertaken to assess the possible impact of the risk. Sensitivity analyses will also be undertaken for the women who were randomised to the conventional care arm, who had a remote blood pressure monitor at home. A post-hoc analysis will be undertaken for aspirin compliance as a modifier based on PFA-100 levels.

Comparison of questionnaires will be made for each time point.

A’within trial’ economic evaluation will be conducted alongside the trial from a health sector perspective, and extending to patient and carer costs. This will combine three forms of complimentary economic analysis in a comprehensive approach.

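### Time to medication institution has no time-to-event rule: if the continuous-outcome rule is applied as written, women who never start drop out and the comparison is no longer randomised

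*Protocol article*

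**What the plan says.** Under Outcome measures, Table 3 of the protocol article lists "Time to medication institution" (in weeks' gestation) among the general secondary outcomes. It does not say which medication is meant, or what value is given to a woman who never starts.

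The section on data handling, analysis and result reporting has two rules for secondary outcomes. For binary ones: "The secondary outcomes that are binary will be analysed using the same methods described for the primary outcomes". For continuous ones: "data that is normally distributed will be analysed with parametric tests and non-normally distributed data will be analysed with non-parametric tests". No time-to-event method or censoring rule appears.

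Three other statements bear on the point:

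- "Data analyses will primarily be carried out according to the intention-to-treat principle", with analyses both with and without imputed data.
- The subgroup list includes "antihypertensive therapy at randomisation", so the plan expects some women to be on treatment at entry.
- Table 1 sets the entry limit as "Before 28 weeks gestation".

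**The concern.** A time in weeks is not binary, so of the two stated rules only the continuous one can take it. That rule chooses a test by the shape of the data, which presupposes one observed value per woman. Here that fails in two ways.

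- Women who deliver without starting have no start week. Eligibility covers IVF pregnancy, autoimmune disease, diabetes, kidney disease and a high-risk first-trimester screen, so this group may be large.
- Women treated before randomisation do have a start week, but it was fixed before allocation. Counting in weeks' gestation rather than from randomisation lets these values into the comparison.

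Starting medication is also an event the intervention could influence. Remote women measure on three occasions a week with clinician review three times a week; controls have a minimum of six additional appointments. Remote monitoring might therefore change who starts as well as when. The starters in the two arms would then be different kinds of women, and a difference between their means would not be a randomised treatment effect.

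**Working it through.** **What the document supplies.** It gives no start rate, start-time distribution or expected effect for this outcome, so there is no stated figure to reproduce for it. The only planned size is 118 per arm for the primary outcome, and that reproduces: (1.645 + 0.842)² × 2 × 0.311 × 0.689 / 0.15² = 117.8, rounded up to 118. I use 118 per arm below only as a realistic group size. Everything else in this section is assumed.

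**1. Constant start rate, cut off at delivery.** Let p be the share of controls who start within a window of T weeks and HR the hazard ratio for remote against control.

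- Control hazard: λ = −ln(1 − p)/T. Remote hazard: HR × λ. Remote share starting: 1 − (1 − p)^HR.
- Mean untreated time within the window, all women: (share starting)/(hazard).
- Mean time to start, starters only: 1/hazard − T × (1 − share)/share.

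Example with p = 0.30, T = 16, HR = 1.5:

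- Hazards 0.0223 and 0.0334 per week; remote share starting 0.414.
- All women: 13.46 − 12.39 = 1.07 weeks.
- Starters only: 7.53 − 7.29 = 0.24 weeks.
- Share of the difference retained: 0.24/1.07 = 0.22.

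**2. Time shift.** Latent start times are normal, delivery is around week 38 (SD 1.5), and every latent start is moved 1 to 3 weeks earlier in the remote arm. Retained share = difference in starters' means divided by the shift.

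| Model | Share of controls starting | Share of difference retained |
|---|---|---|
| Constant hazard, HR 1.25–2.0, T 10–22 weeks | 15% | 0.19–0.20 |
| | 30% | 0.22–0.23 |
| | 50% | 0.27–0.30 |
| | 80% | 0.43–0.51 |
| | 90% | 0.56–0.66 |
| Time shift of 1–3 weeks | 16% | 0.24–0.25 |
| | 26% | 0.30–0.33 |
| | 50% | 0.38–0.45 |
| | 74% | 0.57–0.61 |
| | 90% | 0.72–0.74 |

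**3. Power.** Simulation with 118 per arm, a 20-week window, two-sided 5%, and 34% of controls starting. The 34% borrows the article's 33.8% rate of hypertensive disorders as a rough proxy, which is itself an assumption.

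- HR 1.5: rank test in starters about 6%; log-rank in all women about 52%; rank test in all women with non-starters ranked last, about 50%.
- HR 2.0: rank test in starters about 9%; log-rank in all women about 95%.

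**4. Direction.** Suppose 30% of controls start, at a mean of week 28. Remote care starts the corresponding women at week 27 and adds another 10% who start at week 36. The remote starters' mean is (0.30 × 27 + 0.10 × 36)/0.40 = 29.25 weeks. The remote arm looks 1.25 weeks later, although every woman who would have started under usual care started a week earlier.

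**The case against.** The strongest reply is that the article nowhere says that only starters will be compared. Table 3 lists the outcome, and the analysis section states a general rule without assigning this outcome to it. The statistical analysis plan is not at hand, and a risk set or censoring rule for one of many secondary outcomes is something an article may leave to it. The term non-parametric test could also cover a log-rank test, or a rank test that places non-starters last. Intention to treat is the primary principle, and imputation is foreseen.

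Much of this stands. A reader might infer that the plan commits itself to a starters-only comparison; it does not, and the point has to be conditional. A reader might also infer a fixed loss, such as half of a true difference. The document does not support that either: every input is assumed, and the table shows that about half holds only for particular start rates. In the time-shift model the benchmark also includes latent starts after delivery that would never occur.

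What does not stand is that the stated commitments already solve the problem. Intention to treat keeps a woman in her arm but does not give her a start week. A woman who never starts has no missing date to impute. Ranking non-starters last would need to be stated, and it would still leave in the women treated before randomisation. The article does fix a rule for non-binary secondary outcomes, and that rule does not fit this one.

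**Conclusion.** The point holds in conditional form. Applied as written, the continuous rule would leave out women who never start and admit start dates that predate allocation. The result would be conditioned on a post-randomisation event and could hide or reverse a real difference.

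Neither the size nor the direction can be fixed from this document. As an illustration only, about 0.2 to 0.75 of a true difference is retained when between 15% and 90% of controls start, and attenuation is greatest when few start. These figures rest on the assumed models above and exclude women already treated at entry. The outcome is secondary, so the primary non-inferiority conclusion is unaffected. This is a cheap improvement, not a flaw in the trial's main comparison.

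**What to change.** State for this outcome:

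- Medication means the first antihypertensive, if that is what is intended.
- The analysis set is women not on antihypertensive therapy at randomisation, in the arm to which they were allocated.
- Time runs from randomisation to first antihypertensive, with delivery as a competing event.
- Report cumulative incidence by arm, a hazard ratio adjusted for the minimisation variables, and the proportion ever started.

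If the statistical analysis plan already says this, a cross-reference is enough.

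The cost is a change of method. Antihypertensive use and gestational age at birth are already to be collected, and the outcome itself requires a start date, so no further participants or data items are needed. The downside is that women already treated at entry leave this one secondary analysis.
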